| Clinical Phase:              | Phase I, Safety evaluation                                                                                                                                                                                                                                                                                                                                                                                                                                                                          |
| Background and Rationale:    | The pharmacologically active ingredient of TLN is the membranal lipid Monosialotetrahexosylganglioside or GM1. TLN consists of GM1 associated to a proprietary lipid formulation assembled together as liposomes. Free injections of GM1 have shown to improve the UPDRS-score and therefore the condition of patients with Parkinson's disease. TLN has been developed to improve the delivery of GM1 and its bioavailability and therefore improve the care of Patients with Parkinson's disease. |
| Objective(s):                | The primary objective is: 
 
To demonstrate the safety of TLN administration intravenously in patients with Parkinson's disease.
 
 Secondary objectives are: 
 
Determination of the maximal suitable dose based on safety profile and preliminary efficacy.
 
Determination of the PK profile.
 
                                                                                                  |
| Outcome(s):                  | Primary outcome: Safety, measured as: 
 
Occurrence of AEs
 
Occurrence of SAEs
 
 Secondary outcomes: 
 
Parkinson disease (PD) patients' condition assessed by: Levodopa challenge test (LCT), MDS-UPDRS, PDQ-39, ESS and change in Parkinson's medication (LEDD).
 
Patients' general/mental condition assessed by: BDI, SAS, NMSQuest and MoCA.
 
PK analyses
 
     |

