#### 6.1.1 Dose escalation (Part 1)

In this part a group of 3 patients will receive a single weekly dose that will be increased according to the schedule defined. In parallel, meaning that the first patient will receive a dose X on week Y, if the safety assessment is positive (see **Section 8.3 Dose modifications**) then the following week (Y+1) this patient will receive the next dose (X+1), on that week (Y+1) two other patients will receive the same dose X to confirm the safety assessment. *In fine*, every week patient 1 will receive one dose at the same time that patients 2 & 3 receive the preceding dose.

This weekly increase has been elected to allow rapid determination of the MSD and rapidly reach a dose level that will be beneficial for the patients involved in this trial. This is allowed by the fact that GM1 is expected to be safe and no clear AE are foreseen within this dose range. Furthermore, the 1 + 2 pattern allows one week observation of each dose increase in 1 patient before infusing 2 more.

The first dose level starts at 6 mg which will increase to 12 and 60 mg, then increasing by equal steps of 60 mg up to 720 mg. The escalation will be stopped individually according to the decision matrix detailed in the **Section 8.3 Doses modifications**. The three first steps of the dose are purposely low to account for any possible unexpected effects of the formulation.

Throughout the escalation part, all patients will be monitored twice weekly to record AEs and document them. Monitoring will take place once before each TLN infusion (beginning of the week) and a second time by the end of each week (performed by the principal investigator) to collect AE and allow enough time for the IMC to review them and take their decision on the next infusion/dose modification/delay.

At the end of the escalation, the average of the three maximum tolerated doses by the three patients will be defined as MSD for part 2. With this design, we aim to find the highest dose that generates, if any at all, at maximum only transient mild/moderate AEs. At the same time, this will allow to glean information on clinical effect for the planning of a potential phase II study.

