#### Part 1 – Dose Escalation:

The drug will be administrated in a single ascending dose (SAD) as a once weekly i.v. infusion in 3 patients up to 14 dose levels or until unacceptable toxicity appears (see section **6.1.1 Dose escalation** for details on the sequence between patient 1 and 2/3).

The aim of this dose escalating procedure is to define the MSD in terms of the occurrence of AEs dependent on their seriousness, intensity and causality according to the standards and definitions given in this trial protocol (see section **8.3 Doses modifications**).

|               |        |
|---------------|--------|
| Dose level 1  | 6 mg   |
| Dose level 2  | 12 mg  |
| Dose level 3  | 60 mg  |
| Dose level 4  | 120 mg |
| Dose level 5  | 180 mg |
| Dose level 6  | 240 mg |
| Dose level 7  | 300 mg |
| Dose level 8  | 360 mg |
| Dose level 9  | 420 mg |
| Dose level 10 | 480 mg |
| Dose level 11 | 540 mg |
| Dose level 12 | 600 mg |
| Dose level 13 | 660 mg |
| Dose level 14 | 720 mg |

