#### Part 1 – Dose escalation:

| Causality            | Intensity   | Resolution until next infusion | Next patient added/ Dose increase                                                                                                         |
|----------------------|-------------|--------------------------------|-------------------------------------------------------------------------------------------------------------------------------------------|
| (unlikely/unrelated) | grade 1 - 3 | yes/no                         | yes                                                                                                                                       |
| Possible             | grade 1     | yes                            | yes                                                                                                                                       |
| Possible             | grade 1     | no                             | yes                                                                                                                                       |
| Possible             | grade 2     | yes                            | yes                                                                                                                                       |
| Possible             | grade 2     | no                             | Delay till resolution (maximum of 3 weeks), then rechallenge at same dose level, if re-occurrence stop treatment for the affected patient |
| Possible             | grade 3     | yes/no                         | no (stop treatment for the affected patient but others to continue)                                                                       |
| Probable/definite    | grade 1     | yes/no                         | yes                                                                                                                                       |
| Probable/definite    | grade 2     | yes                            | yes                                                                                                                                       |
| Probable/definite    | grade 2     | no                             | no (stop treatment for the affected patient but others to continue)                                                                       |

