| Probable/definite    | grade 3     | yes                            | stop (for the affected patient but others to continue)                                                                                    |
| Probable/definite    | grade 3     | no                             | Stop for all patients                                                                                                                     |

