- Non-Motor Symptoms Questionnaire (NMSQuest): This questionnaire enables clinicians to complete a comprehensive assessment of a diverse range of non-motor symptoms which can occur in all stages of PD. It is a patient-based screening tool designed to draw attention to the presence of non-motor symptoms in patients for further investigation or treatment. Patients will be asked to give their answer ("ja" or "nein") to 30 questions.
- Levodopa equivalent daily dose (LEDD): LEDD will be assessed at each visit and will be calculated according to Verber *et. al*.
- Pharmacokinetics (PK) of total GM1 in blood over the first 96 h after the first infusion (only in part 2 of the trial):  
The assessment of PK will be determined by the calculation of the Maximum Observed Drug Concentration ( $C_{max}$ ) in plasma, the Time of Maximum Drug Concentration ( $T_{max}$ ) in plasma,  $AUC_{inf}$  in plasma, half-life ( $t_{1/2}$ ) Clearance (CL) and the volume of distribution ( $V_d$ ).  
The predicted half-life of the drug is 30 h according to our pre-clinical data obtained in animals. The blood collection for PK will therefore be performed at the following timepoints after the first infusion (only part 2 of the trial):
  - 0 min (right before the infusion, pre-dose)
  - 5 min before the end of the infusion
  - 30 min after infusion
  - 1 h after infusion
  - 4 h after infusion
  - 24 h after infusion
  - 48 h after infusion
  - 72 h after infusion
  - 96 h after infusion
 Instructions for the collection of blood and the processing and handling are provided in **Annex 3**).
- Determine the maximal suitable dose (MSD): MSD is calculated as the average dose from all maximally reached doses by the 3 patients in the dose escalating part of this trial.

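### The protocol does not say whether the Part 1 stop-all ends Part 1 or the whole trial; if only Part 1, the averaging rules can set the Part 2 dose at, or 20 mg above, the dose that triggered it

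*Protocol*

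**What the plan says.** **The stop.** In the Part 1 table of section 8.3, the row for a probable or definite grade 3 event, unresolved by the next infusion, reads "Stop for all patients". It is the only row that reaches beyond the affected patient. The column is headed "Next patient added/ Dose increase". Section 11.3 sets no statistical stopping rule and points to 8.3 for guidance on stopping individuals, cohorts or the trial as a whole.

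**The stagger.** Section 6.1.1 says that "every week patient 1 will receive one dose at the same time that patients 2 & 3 receive the preceding dose".

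**The Part 2 dose.** Section 6.1.1 says that "the average of the three maximum tolerated doses by the three patients will be defined as MSD for part 2". Section 9.2.2 says "MSD is calculated as the average dose from all maximally reached doses by the 3 patients in the dose escalating part of this trial". Neither makes an exception for a stop-all. Section 8.1.1 has nine patients start on the full MSD once it is defined, weekly for 8 weeks.

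**The purpose.** Section 6.1.1 adds: "we aim to find the highest dose that generates, if any at all, at maximum only transient mild/moderate AEs". Section 8.1.1 says escalation should "define the MSD in terms of the occurrence of AEs dependent on their seriousness, intensity and causality". The Synopsis lists as a secondary objective "Determination of the maximal suitable dose based on safety profile and preliminary efficacy".

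**The concern.** Two things are left open, and they combine. The scope of the stop-all is not stated, so a reader cannot tell whether Part 2 may still open after it. If it may, the only numeric rule for the Part 2 dose is an average that takes no account of why escalation stopped. Because patient 1 runs one level ahead, that patient's higher dose offsets an event in patient 2 or 3, although those two are dosed at the same level precisely to confirm that it is safe.

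At stake is the dose given to nine new patients, eight times each, of a product that section 3.7 describes as given intravenously to humans for the first time. In the Part 2 table of 8.3 the same event stops only the affected patient, so there is no second cohort-level stop.

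**Working it through.** **Inputs.** The dose levels in 8.1.1 are 6, 12 and 60 mg, then steps of 60 mg up to 720 mg at level 14. Both neighbouring steps are therefore 60 mg at levels 4 to 13 (X = 120 to 660 mg). The one-level lead and the tolerated wording come from 6.1.1, and the reached wording from 9.2.2. The protocol gives no figure of its own to reproduce.

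**Main case.** One of patients 2 and 3 has the event at X, the other is unaffected at X, and patient 1 has received X+60 in the same week. Under the tolerated rule I count an affected patient one level lower.

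- Reached: (X + X + X+60)/3 = X+20.
- Tolerated, patient 1 tolerates X+60: (X−60 + X + X+60)/3 = X.
- Tolerated, patient 1 does not tolerate X+60: (X−60 + X + X)/3 = X−20.

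At X = 480 mg:

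- Reached: (480 + 480 + 540)/3 = 500 mg.
- Tolerated: (420 + 480 + 540)/3 = 480 mg, or (420 + 480 + 480)/3 = 460 mg.

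**Edges of the range.**

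- Level 3 (60 mg): reached (60 + 60 + 120)/3 = 80 mg; tolerated (12 + 60 + 120)/3 = 64 mg.
- Level 14, where patient 1 cannot go higher: reached 720 mg; tolerated (660 + 720 + 720)/3 = 700 mg.
- Nothing is claimed for levels 1 and 2.

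**Other configurations**, as the difference from X in mg at levels 4 to 13:

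| Case | Reached | Tolerated |
|---|---|---|
| Patient 1 has the event, others one level below | −40 | −60 |
| Patients 2 and 3 both affected, patient 1 tolerates the next level | +20 | −20 |
| All three dosed at the same level, one affected | 0 | −20 |

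The third row is included because the schedule text after section 8.9 has all three patients start at 6 mg together, unlike 6.1.1.

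If patient 1 had already stopped at a lower level, none of the 91 combinations of trigger level and earlier level is at or above X on either rule. If instead the companion had stopped earlier (levels 4 to 13, 75 combinations), the reached rule gives X in 10 and less than X in 65, and the tolerated rule gives less than X in all 75.

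**The case against.** **The stop-all may cancel Part 2.** Section 11.3 looks to 8.3 for stopping cohorts or the whole trial, and this row is the only candidate there. On that reading no Part 2 dose is ever set. This stands as a possible reading. Against it, the row sits in a table for Part 1 only, under a column about adding patients and raising the dose, and no sentence cancels Part 2.

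**The average may not be meant for this case.** Section 6.1.1 speaks of stopping escalation individually, and the two unaffected patients have not shown a personal maximum. That weakens the tolerated figure, which needs an interpretation. It does not touch the reached rule, since the highest dose received is known whatever the reason for stopping.

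**Aims and safeguards.** The purposes in the Synopsis, 6.1.1 and 8.1.1 argue against such a dose. The IMC must be unanimous on continuing each patient (1.6), so its independent physician can block. The DSMB meets once the MSD is defined (1.7), and the sponsor may terminate (2.9). The DSMB charter and safety management plan are not at hand and may say more. A reader might infer that Part 2 would be protected by discretion alone. That is wrong: 8.3 obliges a stop for any Part 2 patient with a related grade 3 or grade 4 event or a related SAE. But those stops act after dosing, and neither they nor the committees cap the starting dose in the text shown.

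**Averaging tolerates this by design.** If a related grade 3 event at 480 mg resolves and the others reach 720 mg, the reached average is (480 + 720 + 720)/3 = 640 mg. True, and the cap proposed here leaves that alone. The stop-all differs because the protocol itself treats the event as grounds to halt everyone.

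**Conclusion.** The point holds conditionally. The scope of the stop-all is unclear. If it ends only Part 1, the stated rules can return a Part 2 dose of X+20 mg (reached) or X (tolerated, provided patient 1 tolerates the next level; otherwise X−20 mg) at levels 4 to 13. The first two run directly against the aim in 6.1.1, because the triggering event is neither transient nor mild or moderate.

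This rests on the one-level lead in 6.1.1, the event falling in one of patients 2 and 3, and a companion unaffected at the same level. In most of the other configurations checked the average is at or below X, and no probability is attached to any of them.

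A reader might infer that the protocol commits nine patients to a dose above the trigger. The documents do not support that: Part 2 may never open, the tolerated rule does not exceed X at levels 4 to 13, and the committees may intervene. What is missing is a written limit.

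**What to change.** 1. In 8.3, state whether the stop-all ends Part 1 or the trial.
2. If Part 2 may still open, state in 6.1.1 and 9.2.2 that after a stop-all the MSD is the lower of the three-patient average and the dose level immediately below the triggering dose, with no Part 2 if the trigger was level 1. At X = 480 mg this gives 420 mg in the main case.
3. In the Part 2 paragraph of 8.1.1, refer to this rule and have Part 2 wait for the DSMB meeting already scheduled in 1.7. No extra review is needed.

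The cost is a few sentences in an amendment, with no added patients or procedures. The downside is that after such an event Part 2 may start later, at a lower dose, or not at all. The cap also applies in some cases where the average is already below the trigger. When patient 1 has the event at levels 4 to 14, the reached-rule dose falls by a further 20 mg, for example from (480 + 420 + 420)/3 = 440 mg to 420 mg.

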#### Part 2 – Dose consolidation:

| Causality            | Intensity   | Resolution until next infusion | Dose repeat                                                                                                                          |
|----------------------|-------------|--------------------------------|--------------------------------------------------------------------------------------------------------------------------------------|
| (unlikely/unrelated) | grade 1 - 3 | yes/no                         | yes                                                                                                                                  |
| Possible             | grade 1     | yes                            | yes                                                                                                                                  |
| Possible             | grade 1     | no                             | yes                                                                                                                                  |
| Possible             | grade 2     | yes                            | yes                                                                                                                                  |
| Possible             | grade 2     | no                             | Delay till resolution (maximum of 3 weeks), then rechallenge at same level, if re-occurrence stop treatment for the affected patient |

|                   |         |        |                                                                     |
|-------------------|---------|--------|---------------------------------------------------------------------|
| Possible          | grade 3 | yes/no | no (stop treatment for the affected patient but others to continue) |
| Probable/definite | grade 1 | yes/no | yes                                                                 |
| Probable/definite | grade 2 | yes    | yes                                                                 |
| Probable/definite | grade 2 | no     | stop (for the affected patient but others to continue)              |
| Probable/definite | grade 3 | yes    | stop (for the affected patient but others to continue)              |
| Probable/definite | grade 3 | no     | stop (for the affected patient but others to continue)              |

Upon the PIs discretion and dependent on the general state of the patient standard PD medication can be changed during the course of the trial.

#### **8.4 Compliance with study intervention**

Patients will be treated in a clinical practice, in which the investigator can closely follow each patient. Further, the compliance will be assured by medically controlled administration of the IMP.

#### **8.5 Data Collection and Follow-up for withdrawn participants**

If a patient wishes to withdraw his/her consent and prefers to stop his/her participation in this trial (and for all patients with premature withdrawal) she/he will be proposed to undergo both a final assessment (7 days after the last TLN infusion) and follow-up visit (28 days after the last TLN infusion) according to the protocol.

In case patients withdraw their consent, all data collected until the time point of their withdrawal will be kept coded and may be analysed.

#### **8.6 Trial specific preventive measures**

As TLN is expected to have a good safety profile, no trial-specific preventive measures are taken in addition to the usual clinical preventive measures that are already in place.

Patients will receive an emergency contact card (see below) with details on their participation in this trial. Moreover, their general practitioner will receive information from the PI in order to be informed about their patients' participation in this trial. Both measures help creating preventive transparency. In addition, patients will receive a phone number (provided with the patient information and informed consent form, too), where they can reach a member of the trial team reachable 24 h/24 h.

In case of an unexpected medical emergency during a trial visit the patient would be transferred to a nearby located hospital equipped with an emergency unit.

### **8.7 Concomitant Interventions (treatments)**

Patients are asked to continue their usual medications (including anti-parkinsonian medications). The participation in the trial is however not compatible with any other IMP. All medications used to treat PD will be documented in the patient's trial file.

### **8.8 Study Drug Accountability**

The PI or a designee is responsible for drug accountability and record maintenance of the drug accountability log (including date, amount, batch number, expiry date and unique patient number (UPN)) for receipt, use, expiry and destruction of study drug. The drug accountability records must be kept up to date and must be available for monitoring purpose.

### **8.9 Return or Destruction of Study Drug**

Unused or expired medication can only be destroyed at the site after the check of the monitor. Partly unused medication can be destroyed without the check of the monitor. Drug destruction has to be documented on the drug accountability log.

Patients foreseen for part 1 of the trial, will ideally start their trial enrolment and treatment concomitantly. Before the first TLN infusion, patients will be screened for their participation in the trial. If all eligibility criteria are fulfilled, each of the 3 patients will start with an infusion containing 6 mg TLN (day 0). On day 4 they will be assessed according to the description given in chapter 9.3. Procedures at each visit. Only if the criteria as defined in chapter 8.3 Dose modifications are met, the patient can continue to the next dose level which he/she will receive on day 8. All patients will continue in the same manner and receive a weekly infusion of TLN until criteria are met to stop the treatment. Patients have to show up 3 times in week 1 and as of week 2 twice a week. All visits will take place at the Institute of Neurology in Konolfingen.

| Trial Periods                 | Screening | Baseline | Treatment (T) | PK 24h | PK 48h | PK 72h | PK 96h | T | T  | T  | T  | T  | T  | T  | Final assessment | Follow-up |
|-------------------------------|-----------|----------|---------------|--------|--------|--------|--------|---|----|----|----|----|----|----|------------------|-----------|
| Visit                         | 1         | 2        | 3             | 4      | 5      | 6      | 7      | 8 | 9  | 10 | 11 | 12 | 13 | 14 | 15               | 16        |
| Time (weeks)                  | -4 to -1  | 1        | 1             | 1      | 1      | 1      | 1      | 2 | 3  | 4  | 5  | 6  | 7  | 8  | +1               | +4        |
| Time (days)                   | -28 to -1 | 0        | 1             | 2      | 3      | 4      | 5      | 8 | 15 | 22 | 29 | 36 | 43 | 50 | +7               | +28       |
| Patient information & consent | x         |          |               |        |        |        |        |   |    |    |    |    |    |    |                  |           |
| In-/Exclusion Criteria        | x         |          |               |        |        |        |        |   |    |    |    |    |    |    |                  |           |
| Pregnancy Test                | x         |          |               |        |        |        |        |   |    |    |    |    |    |    |                  |           |
| Medical History               | x         |          |               |        |        |        |        |   |    |    |    |    |    |    |                  |           |
| Clinical Assessment           | x         |          |               |        |        |        |        |   |    |    |    |    |    |    | x                | x         |
| Vital Signs                   | x         | x        | x             |        |        |        |        | x | x  | x  | x  | x  | x  | x  | x                | x         |
| MoCA                          | x         |          |               |        |        |        |        |   |    |    |    |    |    |    | x                |           |
| Lab tests                     | x         | x        |               |        |        |        |        | x | x  | x  | x  | x  | x  | x  | x                | x         |
| Levodopa Challenge Test       |           | x        |               |        |        |        |        |   |    |    |    |    |    |    | x                |           |
| TLN Infusion                  |           |          | x             |        |        |        |        | x | x  | x  | x  | x  | x  | x  |                  |           |
| Blood collection (PK)         |           |          | x             | x      | x      | x      | x      |   |    |    |    |    |    |    |                  |           |
| MDS-UPDRS                     |           |          | x             |        |        |        |        | x | x  | x  | x  | x  | x  | x  | x                | x         |
| PDQ-39                        |           | x        |               |        |        |        |        |   |    |    |    |    |    |    | x                |           |
| ESS                           |           | x        |               |        |        |        |        |   |    |    |    |    |    |    | x                |           |
| BDI                           |           | x        |               |        |        |        |        |   |    |    |    |    |    |    | x                |           |
| SAS                           |           | x        |               |        |        |        |        |   |    |    |    |    |    |    | x                |           |
| NMSQuest                      |           | x        |               |        |        |        |        | x | x  | x  | x  | x  | x  | x  | x                |           |
| LEDD                          |           | x        |               |        |        |        |        | x | x  | x  | x  | x  | x  | x  | x                | x         |
| Adverse events recording      |           |          | x             | x      | x      | x      | x      | x | x  | x  | x  | x  | x  | x  | x                | x         |

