Safety lab values will be assessed from blood collection performed every week during part 1 (3 days after TLN infusion) and part 2 (on the day of TLN infusion) according to the schedule. Abnormal

values will be compared to the normal range provided by the laboratory (**Annex 2**), then assessed by the PI for grading. All analyses will be performed from venous blood collection before the infusion. Samples will be collected on each sampling day by courier by Viollier and processed in their facilities.

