9.3.2 Visit 2: Baseline (day 0)

- Vital signs
- Full lab tests
- LCT
- PDQ-39
- ESS
- BDI
- SAS
- NMSQuest
- LEDD

9.3.3 Visit 3, 5, 7, 9, 11 and every other visit until visit 29: Treatment

- Vital signs
- TLN Infusion
- MDS-UPDRS (Part III before the infusion; Part I, II and IV during the infusion; Part III again after the infusion)
- AE recording

9.3.4 Visit 4, 6, 8, 10, 12 and every other until visit 28: Assessment

- Vital signs
- Full lab test
- NMSQuest
- LEDD
- AE recording

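### The Part 1 summary starts all three patients together, against the 1+2 stagger in 6.1.1; and under the stagger the 9.3 visit list gives patient 1 no safety visit between 720 mg and the day patients 2 and 3 are due it

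*Protocol*

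**What the plan says.** Section 6.1.1 of the Protocol gives patient 1 a dose in one week and patients 2 and 3 the same dose a week later, after a positive safety assessment. The stated reason is that "the 1 + 2 pattern allows one week observation of each dose increase in 1 patient before infusing 2 more". The same section requires two checks a week: "Monitoring will take place once before each TLN infusion (beginning of the week) and a second time by the end of each week". The second leaves the Internal Monitoring Committee (IMC) time to review before the next infusion. Section 8.1.1 points back to 6.1.1 "for details on the sequence between patient 1 and 2/3".

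The Part 1 summary printed after section 8.9 reads differently: "Patients foreseen for part 1 of the trial, will ideally start their trial enrolment and treatment concomitantly". It goes on that "each of the 3 patients will start with an infusion containing 6 mg TLN (day 0"), with an assessment on day 4, and that, if the section 8.3 criteria are met, "the patient can continue to the next dose level which he/she will receive on day 8". It does not mention waiting for patient 1.

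On timing, section 9.2.1 states: "Safety lab values will be assessed from blood collection performed every week during part 1 (3 days after TLN infusion"). Section 9.3.3 is headed "Visit 3, 5, 7, 9, 11 and every other visit until visit 29: Treatment". Section 9.3.4 lists assessment visits at even numbers from 4 to 28, section 9.3.5 makes visit 30 the final assessment 7 days after the last infusion, and section 9.3.6 makes visit 31 the follow-up.

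**The concern.** The one-week lead of a single patient is the main safeguard for escalating every week with a product that has never been given to humans (sections 3.4 and 3.7). A site working from the Part 1 summary would dose all three patients at each new level at once, each advancing on that patient's own criteria, and the lead would vanish.

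A site that keeps the stagger but books visits from section 9.3 meets a different gap. After the 14th infusion no end-of-week assessment is listed. Patient 1 is the one whose data decide whether patients 2 and 3 go to 720 mg, so the check is missing for the patient and dose at which that gate depends on it.

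**Working it through.** **Dose levels.** Section 8.1.1 lists 6 mg, 12 mg, then 60 to 720 mg in steps of 60: 2 + 12 = 14 levels.

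**Visits in section 9.3.**
- Treatment, odd visits 3 to 29: (29 − 3)/2 + 1 = 14. This reproduces the 14 levels.
- End-of-week assessment, even visits 4 to 28: (28 − 4)/2 + 1 = 13.
- Visits 29, 30 and 31 are infusion 14, final assessment and follow-up. No number is free between infusion 14 and the final assessment.

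**Calendar**, with patient 1's first infusion as day 1:
- Infusion k falls on day 1 + 7(k − 1), so infusion 14 (720 mg) is on 1 + 13 × 7 = day 92.
- The labs promised by 9.2.1 would fall on 92 + 3 = day 95. No visit is listed there.
- Visit 30 falls on 92 + 7 = day 99.
- Patients 2 and 3 run 7 days later, so their 720 mg infusion is on 92 + 7 = day 99.

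**Time from patient 1's check to the infusion of patients 2 and 3 at the same level**, allowing ±1 day on each visit (section 9.3):

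| Levels | Patient 1's check | Patients 2 and 3 infused | Nominal margin | With windows |
|---|---|---|---|---|
| 1 to 13 (level 1 shown) | day 4 | day 8 | 4 days | 2 to 6 days |
| 14 | day 99 | day 99 | 0 days | −2 to +2 days |

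Section 9.3.3 lists no labs at treatment visits. Patient 1's first labs after 720 mg would therefore be drawn at visit 30 and sent by courier to the outside laboratory.

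**Under the Part 1 summary** the lag is 0 days, and at none of the 14 levels does patient 1 have a visit before patients 2 and 3 receive the same dose.

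**The day 0 label.** Day 0 is the baseline visit (9.3.2). An infusion on day 0 puts the day-4 assessment 4 days later and the day-8 dose 8 days later. An infusion on day 1 gives 3 and 7 days, which matches the labs in 9.2.1 and weekly dosing. Day 1 is evidently what was meant.

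**Two smaller points.** Section 1.7 schedules DSMB meetings after levels 5, 10 and 15. There are 14 levels, so one of the three level-based meetings cannot occur. Separately, 6.1.1 says every increment is split 1+2, but under the 8.3 matrix patient 1 can be stopped while the others carry on, and no new leader is named.

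**The case against.** The stagger is set out at length in 6.1.1, cross-referenced in 8.1.1 and implied by the Part 1 matrix in 8.3, whose outcome column covers adding the next patient as well as raising the dose. The summary's sentence is qualified by the word ideally, and its day numbers could be each patient's own clock. The IMC must also agree unanimously on each patient. All this shows which text should prevail. It does not reconcile the two, because the ideal the summary states is the reverse of the safeguard.

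On the visit list, the Part 1 schedule table (Table 1) could not be read in the copy available and might show the visit. Sections 6.1.1 and 9.2.1 and the Part 1 summary all call for the check in general terms. Visit 29 itself records adverse events and vital signs, patients are asked to report events between visits, and the IMC in principle meets weekly. The step from 660 to 720 mg is about 9% (60/660), and it arises only if patient 1 reaches level 14. These points limit the harm and show that 9.3 is the part in error. They do not create a visit: consecutive numbering from 29 to 31 leaves no place for one, and visit 29 is the day of the infusion.

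The day 0 slip is no larger than the ±1 day window. The DSMB slip loses little, because the board also meets once the maximal suitable dose is defined and can then cover levels 11 to 14.

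**Conclusion.** The concern holds and should be fixed. Its two limbs are alternatives, depending on which text a site follows.

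- If the Part 1 summary is followed, patients 2 and 3 have 0 days of lead from patient 1 instead of 7, at every level.
- If the stagger is followed with the 9.3 list, the nominal margin at 720 mg is 0 days instead of 4 (−2 to +2 with windows). One gate is affected, through patient 1 only.

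The first limb rests on the text alone. The second rests on the 9.3 headings and their numbering, on nominal weekly dosing, and on patient 1 reaching level 14 without delay. The DSMB level and the missing rule for a successor leader are minor.

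**What to change.** - Reword the Part 1 summary: patient 1 is infused on day 1, and patients 2 and 3 start one week later after IMC release, as in 6.1.1.
- Add to 9.3.4 an end-of-week assessment with full labs after infusion 14 (day 95), at least for patient 1. Require IMC review of it before level 14 is released to patients 2 and 3. Check the schedule table against the change.
- In 1.7, replace DSMB level 15 with a level that exists: 14, or 13 if review is wanted before the top dose.
- State that if patient 1 stops, one remaining patient becomes the leader, so that increments stay staggered.

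The cost is wording in the Protocol and the DSMB charter, plus one short visit for patient 1 (three if all Part 1 patients have it). Sections 6.1.1 and 9.2.1 already commit the trial to that visit.
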